#### Statistical analyses

2.8.7

##### Efficacy assessment

2.8.7.1

For the efficacy assessment of this trial, both ITT and per-protocol (PP) analyses will be performed. Missing data will be adjusted using the last-observation-carried-forward (LOCF) imputation method on ITT analysis. The continuous variables will be expressed as the mean ± SD and the nominal variables will be reported as percentages. The ITT method will include all randomized subjects, regardless of any protocol violations or trial dropouts. The PP method will include only the subjects who have completed the whole study period without any major protocol violations and who have medication compliance rate equal to or greater than 70%. Missing values from the efficacy analysis will be modulated by applying the LOCF. The baseline demographic information will be compared by either a chi-square test for nominal variables or an analysis of variance (ANOVA) for continuous variables. For the within-group analysis, the primary and secondary outcome variables will be assessed using a paired *t* test. The between-groups analysis after 8 weeks of administration will be performed using a repeated-measure ANOVA for the primary outcome variables, and a paired *t* test for the mean difference in the VAS score between the SDT and placebo groups. As a secondary outcome variable, the mean differences in ST and WHOQOL-BREF scores between the groups will be analyzed using a repeated-measure ANOVA for ST and an ANOVA and post-hoc analysis for the WHOQOL-BREF scores. For all non-normal distribution data, a nonparametric statistical test will be performed. SPSS for Windows version 25.0 (SPSS Inc., Chicago, IL) will be used for statistical analysis. The statistical significance level will be set at *P* < .05.

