#### Participant withdrawal criteria

2.3.3

The trial would be discontinued if participants met any of the criteria summarized in Table 2. The subjects who are withdrawn after randomization will be followed-up for outcomes. Reasons for withdrawal will be documented in case report forms (CRFs) and data will be analyzed using the intention-to-treat (ITT) principle. Each site clinical research coordinator will be responsible for making next visit reminder phone calls to prevent participant dropout.

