#### Compliance calculation

2.8.4

At visit 2 and 3, a bag of IP, which includes 93 aluminum foil packages, will be provided to the subjects. They will be asked to return the remaining investigational medications. The rate of compliance will be calculated as compliance (%) = ([93 - remaining products]/expected intake) × 100. Clinical trials will be continued only if compliance is equal to or greater than 70%.^[16]^

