#### Sample size calculation

2.8.6

The change in the CHHF VAS score between baseline and post treatment will be used as the primary outcome measure. The hypothesis is follows: 
[figure not shown]

Δ1: Mean change in the CHHF VAS score between baseline and post treatment in the UCHA group

Δ2: Mean change in the CHHF VAS score between baseline and post treatment in the placebo group

Based on the prior research,^[14]^ the expected mean CHHF VAS score difference in the SDT group is 10.93, and the pooled standard deviation (SD) is estimated to be 22.28. Considering a dropout rate of 20%, we determine to recruit 82 subjects per arm to calculate the treatment efficacy and to offer the power calculation for a future large-scale RCT. Each site will recruit the participants competitively.

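### LOCF is the only stated missing-data method for the ITT analysis with 20% dropout planned, so the week-8 VAS difference can be biased, in a direction set by the dropout pattern

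*Protocol article*

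**What the plan says.** Section 2.8.7.1 of the protocol article names LOCF twice: "Missing data will be adjusted using the last-observation-carried-forward (LOCF) imputation method on ITT analysis", and later "Missing values from the efficacy analysis will be modulated by applying the LOCF". It names no other method. The same section defines the analysis set: "The ITT method will include all randomized subjects, regardless of any protocol violations or trial dropouts".

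Section 2.8.6 sets the endpoint, "The change in the CHHF VAS score between baseline and post treatment will be used as the primary outcome measure", and the allowance for loss: "Considering a dropout rate of 20%, we determine to recruit 82 subjects per arm". Section 2.2 schedules visits at 4-week intervals over 8 weeks of treatment.

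Two further statements bear on which values will be missing. Section 2.3.3 says: "The subjects who are withdrawn after randomization will be followed-up for outcomes". Section 2.8.4 says: "Clinical trials will be continued only if compliance is equal to or greater than 70" per cent.

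**The concern.** A missing week-8 VAS can be filled only from baseline or week 4. A participant who leaves before week 4 is scored as exactly zero change. One who leaves after week 4 is frozen at whatever response had been reached by then. If VAS moves over the 8 weeks in either arm, placebo included, these are not plausible week-8 values, and the error differs between arms when the amount or timing of loss differs.

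At the planned rate this touches 0.20 × 82 = 16.4, about 16 participants per arm, on the primary outcome. Section 2.8.6 also says that the trial is to support the power calculation for a later large trial, so a distorted difference would carry into that trial's sample size.

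**Working it through.** **Inputs from the article.** Difference 10.93 mm and pooled SD 22.28 mm (2.8.6, where the group is labelled SDT; taken here as the planning difference for UCHA); 20% dropout and 82 per arm (2.8.6); significance level 0.05 (2.8.7.1); 1:1 allocation (2.4). Power and sidedness are not in the readable text. Two-sided 5% and 80% power are assumed because they reproduce the stated size.

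**The plan's own figure.** n = 2 × (1.960 + 0.842)² × 22.28² / 10.93² = 65.23 per arm; 65.23 / 0.8 = 81.5, so 82. (Rounding up to 66 first gives 82.5, so 83.) The stated 82 is reproduced. With 66 observed per arm, power is 80.5%.

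**Assumptions not in the article.** Half of the week-8 change is present at week 4. Half of the leavers carry baseline and half carry week 4. Leavers would have had the same mean week-8 change as the others in their arm. For unequal loss, the placebo arm improves by 15 mm, so the UCHA arm improves by 25.93 mm.

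**Expected LOCF change in an arm with loss p.** Change × m(p), where m(p) = (1 − p) + (p/2) × 0.5 + (p/2) × 0 = 1 − 0.75p.

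**Equal 20% loss.** m = 0.85, so 10.93 × 0.85 = 9.29 mm, 15% too small. If all leavers carry baseline: 10.93 × 0.80 = 8.74 mm. If all carry week 4: 10.93 × 0.90 = 9.84 mm. The placebo change cancels here.

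**Unequal loss (UCHA / placebo).**
- 30% / 10%: 25.93 × 0.775 − 15 × 0.925 = 20.10 − 13.88 = 6.22 mm.
- 10% / 30%: 25.93 × 0.925 − 15 × 0.775 = 23.99 − 11.63 = 12.36 mm.
- 25% / 15%: 25.93 × 0.8125 − 15 × 0.8875 = 21.07 − 13.31 = 7.76 mm.
- 15% / 25%: 25.93 × 0.8875 − 15 × 0.8125 = 23.01 − 12.19 = 10.83 mm.
- No true effect, 30% / 10%: 15 × (0.775 − 0.925) = −2.25 mm.
- No true effect, equal loss: 0.

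**Precision and power.** SE with 82 values per arm: 22.28 × √(2/82) = 3.48. SE with 66 observed per arm: 22.28 × √(2/66) = 3.88. The ratio is 0.90, so the printed SE is about 10% smaller. LOCF analyses all 82 per arm, so at 9.29 mm: 9.29 / 3.48 = 2.67; 2.67 − 1.96 = 0.71; power about 76%.

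**Simulation check.** 82 per arm, 6,000 runs, visit correlation 0.5, dropout at random, a 20 mm placebo change instead of 15, other assumptions as above.

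| Loss UCHA / placebo | True difference | LOCF mean | LOCF coverage | LOCF rejection rate |
|---|---|---|---|---|
| 20% / 20% | 10.93 | 9.25 | 92.6% | 74.2% |
| 30% / 10% | 10.93 | 5.35 | 65.3% | 32.0% |
| 10% / 30% | 10.93 | 13.07 | 90.9% | 96.0% |
| 20% / 20% | 0 | 0.01 | 95.3% | 4.7% |
| 30% / 10% | 0 | −3.00 | 86.2% | 13.8% |
| 10% / 30% | 0 | 3.06 | 85.0% | 15.0% |

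Using observed week-8 values only, the first row becomes mean 10.88, coverage 95.1% and power 79.2%. In that row the LOCF model SE (3.54) matches the estimator's own sampling SD (3.53), so the coverage loss comes mainly from bias.

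**The case against.** **The bias is conditional.** A reader might infer that the week-8 effect is necessarily biased. The documents do not support that. With equal loss and no true effect there is none, and with equal loss and a true effect the bias is toward zero. The larger distortions need an assumed threefold imbalance in loss and an assumed placebo change. At 15% / 25% the result is 10.83 mm, almost the true value. This objection stands, and the point is that the difference can be biased.

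**Power does not fall to 66%.** Putting 9.29 mm on 66 per arm gives that figure, but it charges the dropout twice, because LOCF keeps all 82 in the analysis.

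**The LOCF standard error is not too small for LOCF itself.** It matches that estimator's variability. What holds is narrower: imputed values are counted as observed.

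**Sections 2.3.3 and 2.8.7.1 need not conflict.** A VAS collected after withdrawal is not missing, so LOCF may cover only what follow-up fails to obtain, and true missingness may then be below 20%. The article does not say so, but a contradiction is not shown. Nor is it shown that the 70% rule in 2.8.4 creates missing outcomes: that sentence does not mention outcome visits, and the content of Table 2 is not visible.

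**Leavers may not share the change of those who stay.** If they drifted back toward baseline, carrying baseline forward would be less wrong. That argues for measuring those values, as 2.3.3 promises, not for assuming them.

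**This is a condensed article on a pilot trial.** Sensitivity analyses may sit in an unseen analysis plan. The article nevertheless states LOCF as the ITT method, so this is a method chosen, not a detail left out. The per-protocol analysis is no safeguard, since it keeps only compliant completers.

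**Conclusion.** The point holds in conditional form: with LOCF as the only stated ITT method, the primary week-8 difference can be biased, and the sign depends on how much each arm loses and when. With equal 20% loss, a true 10.93 mm becomes about 9.3 mm (8.7 to 9.8), and power is about 74% to 76% against about 80%. With imbalances between 30% / 10% and 10% / 30% and a 15 mm placebo change, it ranges from about 6.2 to 12.4 mm, and a false −2.3 mm can appear when there is no effect. LOCF therefore cannot be defended as always conservative. The week-4 fraction, dropout timing, imbalance and placebo change are assumptions; the article gives none of them. The change should be made, but nothing here invalidates the design or the sample size.

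**What to change.** - State in 2.8.7.1 that every observed week-4 and week-8 VAS enters the ITT analysis, including values collected after withdrawal under 2.3.3.
- Make the primary ITT analysis a likelihood-based mixed model with baseline VAS, hospital, group, visit and group-by-visit, reporting the week-8 contrast; or use multiple imputation. Both rest on missingness at random given the observed data, so retrieving post-withdrawal values remains the main protection.
- Keep LOCF at most as a sensitivity analysis.
- Reconcile the 70% compliance sentence in 2.8.4 with the outcome follow-up in 2.3.3, so that sites and the statistician know which outcome values are expected. Which compliance rule applies is for the sponsor and investigators.

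The cost is analysis wording. The mixed model runs in the named SPSS version, no visits are added beyond the follow-up already promised, and 82 per arm stands. Intervals may be slightly wider than LOCF would show. Section 2.9 places data entry after trial completion, so the wording can be changed before database lock.

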### Randomization

2.4

Suitable participants, who agree to participate in this RCT, will be randomly assigned to a UCHA group or a placebo group at a 1:1 ratio. A total of 164 eligible participants each will be allocated to the UCHA and placebo groups. An internet-based research randomizer (IRR) developed by the contract research organization (CRO), the Institute of Safety and Effectiveness Evaluation for Korean Medicine (ISEE), will perform the assignment. A random order will be generated by the CRO's independent professional statistician using the R software (The R Foundation for Statistical Computing, Vienna, Austria) and stratified by the hospital using random block sizes of 2 and 4 based on the allocation code provided by the R software.

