##### VAS

2.8.1.1

The VAS score (ranging from 0 mm as no discomfort to 100 mm as the maximum coldness imaginable) will be used to assess the severity of CHHF at every visit.^[14]^

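### The primary VAS outcome is given two between-group tests with neither designated as decisive: a repeated-measures ANOVA not tied to the contrast the trial was sized on, and a paired t test that cannot compare two independent arms

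*Protocol article*

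**What the plan says.** Section 2.8.6 (Sample size calculation) fixes one outcome: "The change in the CHHF VAS score between baseline and post treatment will be used as the primary outcome measure". The hypothesis compares its mean in the UCHA arm with its mean in the placebo arm. The planning figures are "the expected mean CHHF VAS score difference in the SDT group is 10.93" and "the pooled standard deviation (SD) is estimated to be 22.28", followed by "Considering a dropout rate of 20%, we determine to recruit 82 subjects per arm".

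Section 2.8.7.1 (Efficacy assessment) gives the analysis: "The between-groups analysis after 8 weeks of administration will be performed using a repeated-measure ANOVA for the primary outcome variables". The same sentence continues with a second between-group test, a paired t test of the mean VAS difference between SDT and placebo. The section ends with a general rule, "For all non-normal distribution data, a nonparametric statistical test will be performed", and a single significance level of P < .05.

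Two other sections bear on this. Under Randomization, patients "will be randomly assigned to a UCHA group or a placebo group at a 1:1 ratio". Under VAS, the scale "will be used to assess the severity of CHHF at every visit", and the design section sets visits every 4 weeks through week 8 plus a follow-up 4 weeks later.

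**The concern.** One outcome has two between-group tests at the same level, and no sentence says which settles the primary question. Each has its own defect.

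- **The ANOVA.** The text does not fix which visits enter or which effect is read. Over several visits, the group effect averages the arms' difference across time, including baseline, where no treatment effect is possible. The group-by-time test is an omnibus test that responds to a difference in pattern at any visit. Neither is the week-8 contrast of section 2.8.6.
- **The t test.** This is the test aimed at the sized contrast, but it is described as paired. Patients in two randomised parallel arms have no pairs. It also names SDT, an arm this trial does not have.

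At stake is whether the primary conclusion answers the question the trial was sized for, and whether it can be chosen from several P values after the fact.

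**Working it through.** **Step 1: reproduce the sample size.** Inputs from section 2.8.6: difference 10.93 mm, SD 22.28 mm (read as the SD of the change), dropout 20%. Assumed, because the article does not state them: two-sided 5% and 80% power.

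n per arm = 2 × [22.28 × (1.960 + 0.842) / 10.93]² = 65.23. Dividing by 0.8 gives 81.5, so 82. The stated 82 per arm is therefore what a two-sample test of the baseline-to-week-8 change needs. With 66 completers per arm the t-based power is 79.9%.

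**Step 2: when does the ANOVA match that test?** With baseline and week 8 only, the group-by-time F test is algebraically the two-sample t test on change; simulated P values agreed to about 1e-15. The group effect from the same two visits is a different test, with 22% to 54% power over correlations 0.7 to 0.3.

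**Step 3: add week 4.** Assumptions not in the document: equal correlation ρ between visits, 0.3 to 0.7; SD of change held at 22.28; 66 per arm; true differences 0 / 5.465 / 10.93 mm at baseline / week 4 / week 8.

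Group-by-time: noncentrality λ = (n/2) × Σ(dᵢ − d̄)² / (22.28²/2).
- Σ(dᵢ − d̄)² = 2 × 5.465² = 59.73, and 22.28²/2 = 248.2.
- λ = 33 × 59.73 / 248.2 = 7.94.
- The t test on change has the same noncentrality, [10.93 / (22.28 × √(2/66))]² = 2.818² = 7.94, but spends 1 degree of freedom instead of 2.
- Power: **70.9%** for group-by-time against **79.9%** for the change. ρ cancels.

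Group effect: mean difference 5.465 mm; variance of a patient's mean = [248.2/(1 − ρ)] × (1 + 2ρ)/3; SE = √(2 × variance / 66).

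| ρ | SE (mm) | 5.465 / SE | Power |
|---|---|---|---|
| 0.3 | 2.394 | 2.283 | 62% |
| 0.5 | 3.167 | 1.726 | 40% |
| 0.7 | 4.478 | 1.220 | 23% |

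If follow-up also enters, with an assumed half effect there, the powers are 65% for group-by-time and 23% to 67% for the group effect.

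**Step 4: significance without a week-8 difference.** Suppose the arms differ by 10.93 mm at week 4 and by nothing at week 8. Then Σ(dᵢ − d̄)² = 10.93² × 2/3 = 79.64, λ = 33 × 79.64 / 248.2 = 10.59, and group-by-time is significant **83%** of the time. The t test on change stays at 5%.

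**Step 5: error rate under the null.** Simulation with three visits, 66 per arm, ρ 0.3 to 0.7, 40,000 runs for each ρ, and an ordinary independent-groups t test standing in for the paired one:
- t test or group-by-time below .05: 7.4% to 7.6%.
- t test, group-by-time or group effect below .05: 12.0% to 12.1%.

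**Step 6: the paired test taken literally.** Pairing the arms in arbitrary row order gave about 5% error under the null and, in the three-visit setting of Step 3, 79% to 81% power. The harm is therefore not in average operating characteristics. The P value depends on an arbitrary ordering of patients, and the test cannot be run on everyone when the arms differ in size.

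**The case against.** **The ANOVA may be the right test.** The quoted sentence ties it to 8 weeks of administration, and the outcome is a two-point change. On baseline and week 8, read on group-by-time, it is exactly the planned test. A reader might infer that the ANOVA does not test the week-8 difference at all. The document does not support that, because it never says that week 4 or follow-up enters the model. What stands is that the ANOVA is not tied to the contrast. The multi-visit reading is the more natural one: VAS is taken at every visit, and with two visits only, the second between-group test would be redundant.

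**These are SAP details.** Visits and effect could be settled in a SAP. Two tests without a hierarchy, and a paired test across independent arms, are statements of this document that a SAP could only override.

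**The nonparametric rule.** One might also fault it as a data-driven switch. The condition is stated in advance, and the criterion and choice of test are ordinary SAP content. Adding a rank test as a free alternative raised the null rate only from 7–9% to 8–9% with three or four visits. It does not carry the point.

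**The wrong effect passed on.** A reader might infer that the future trial would inherit an effect other than the one sized here. That does not follow, since means and SDs are to be reported whichever P value leads.

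**The 66 per arm.** The ITT analysis with LOCF would include all 82. Without dilution by LOCF, power would be 88% for the change and 81% for three-visit group-by-time. The levels rise, but the gap remains.

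**Exploratory status.** The trial is called a pilot and the inflation is modest. This lowers the severity but does not remove the error.

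**Conclusion.** Wrong as written, at moderate severity. Two faults rest on the text alone: two between-group tests of one primary outcome with neither designated as decisive, and a paired test naming SDT for what are independent UCHA and placebo arms. The sample size itself is not at fault.

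The size of the ANOVA problem is conditional. It is nil under the two-visit, group-by-time reading. With week 4 included it is a loss of about 9 percentage points of power for group-by-time and far more for the group effect. The 83% figure needs a full effect at week 4 that vanishes by week 8; it shows what the omnibus test responds to and is not a forecast. The null-error figures, about 7.5% and 12%, assume that any listed P value may be claimed and that the t test is run as an independent-groups test.

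**What to change.** In section 2.8.7.1, name one primary analysis: the UCHA-minus-placebo difference in VAS change from baseline to week 8, with a 95% CI, from an independent-groups comparison. ANCOVA adjusting for baseline VAS is preferable; the week-8 contrast of a mixed model is an acceptable alternative. Replace the paired t test between SDT and placebo with this comparison between UCHA and placebo. Label the repeated-measures ANOVA as supportive and any rank test as a sensitivity analysis.

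The cost is wording only: 82 per arm, the visits and the data collected are unchanged. The one loss is that the ANOVA result can no longer be quoted as primary. The article reports recruitment still under way, with 72 enrolled, and analysis only after database lock, so on that status the choice can be fixed before results by arm are seen.

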### Study design and setting

2.2

This pilot, randomized, double-blind, placebo-controlled, parallel-group, multi-center clinical trial will be conducted in 5 university-affiliated Korean medicine hospitals, namely Gachon University Gil Korean Medical Hospital, Korean Medical Hospital of Sangji University, Semyung University Second Affiliated Korean Medical Hospital at Chungju, Kyung Hee University Korean Medical Center, and Kyung Hee University Korean Medicine Hospital at *Gangdong*.

Written informed consent will be obtained from the subjects, after giving detailed explanation and they will be screened up to 7 days prior to randomization. Once assigned to the subject identifier, they will be administered investigational products (IPs) for 8 weeks and asked to visit the enrolled trial site every 4 weeks for efficacy and safety examination. At 4 weeks after post treatment visit, follow-up visit will be scheduled. The participants will be asked to return any remaining IPs at each visit to monitor adherence, in order to calculate medication compliance. During the trial, the participants will be prohibited from administering any medications which can impact CHHF. The methodology of the trial is based on the consolidated standards of reporting trials guidelines and standard protocol items: recommendations for interventional trials checklist (see additional file 1). Table 3 presents a schematic flow diagram of the study.

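### One of the two between-group VAS analyses is a paired t test, although the arms are independent and no pairs exist

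*Protocol article*

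**What the plan says.** Section 2.2 describes the design as "This pilot, randomized, double-blind, placebo-controlled, parallel-group, multi-center clinical trial". In section 2.4 participants "will be randomly assigned to a UCHA group or a placebo group at a 1:1 ratio", stratified by hospital, in blocks of 2 and 4. Section 2.8.6 fixes the endpoint: "The change in the CHHF VAS score between baseline and post treatment will be used as the primary outcome measure". Its hypothesis is framed on the mean change in the UCHA group (Δ1) and in the placebo group (Δ2).

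Section 2.8.7.1 then uses the paired t test twice. The first use is within arms: "For the within-group analysis, the primary and secondary outcome variables will be assessed using a paired *t* test". The second is between arms. The sentence begins "The between-groups analysis after 8 weeks of administration will be performed using a repeated-measure ANOVA for the primary outcome variables" and continues "and a paired *t* test for the mean difference in the VAS score between the SDT and placebo groups". SDT is not an arm of this trial; the arms are UCHA and placebo.

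**The concern.** A paired t test needs a one-to-one link between the two observations in each pair. Within an arm that link is the participant, measured before and after treatment. Between arms there is none: the article describes no matching and no crossover. Blocked randomisation does not supply it either. A block of 4 has no unique pairing, and nothing treats a block of 2 as a matched pair.

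The mean difference is the same however participants are paired, but its standard error is not. Two analysts with the same data could report different confidence intervals and P values. If the arms differ in size, the unpaired remainder must be left out. That is likely in the per-protocol set, which is restricted to completers without major violations and with at least 70% compliance. The clause matters because it concerns the mean VAS difference between arms, which is close to the Δ1 and Δ2 contrast of the stated hypothesis.

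**Working it through.** **Inputs.** From section 2.8.6: expected difference 10.93, pooled SD 22.28, dropout 20%, 82 per arm. From section 2.8.7.1: significance at P < .05. Assumed, because the article does not state them: two-sided testing and 80% power.

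**Step 1: reproduce the plan's sample size.** For two independent samples,

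n = 2 × [SD × (1.960 + 0.842) / difference]² = 2 × [22.28 × 2.802 / 10.93]² = 65.2 per arm.

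Allowing for dropout, 65.2 / 0.8 = 81.5, so 82, the stated figure (83 if 65.2 is first rounded up to 66). The paired formula, with 22.28 taken as the SD of the paired differences, has no factor 2 and gives 32.6, about 33. The planned number therefore fits an independent-samples comparison.

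**Step 2: the valid test at 66 evaluable per arm.** SE = 22.28 × √(2/66) = 3.88, with 130 degrees of freedom.
- Observed difference 7.7 (chosen to be borderline): t = 7.7 / 3.88 = 1.985, P = 0.049, 95% CI half-width 7.67 mm.
- Observed difference 10.93: t = 2.82, P = 0.0056.

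**Step 3: what arbitrary pairing does.** With equal SDs the paired SE is 3.88 × √(1 − r), where r is the chance correlation created by the pairing, with 65 degrees of freedom. Over random pairings r has mean 0 and SD 1/√65 = 0.124, so its central 95% is about ±0.24. The SE then runs from 3.88 × √0.76 = 3.38 to 3.88 × √1.24 = 4.32.

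**Step 4: simulation.** One fixed data set per scenario, 66 per arm, SD 22.28 in each arm, 20,000 random pairings:

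| Observed difference | Two-sample P | Paired P, central 95% | Paired P, extremes | Pairings with P < 0.05 |
|---|---|---|---|---|
| 7.7 | 0.049 | 0.026 to 0.079 | 0.008 to 0.104 | 46% |
| 10.93 | 0.0056 | 0.0019 to 0.0140 | 0.0003 to 0.023 | 100% |

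For the 7.7 mm case the CI half-width runs from 6.73 to 8.63 mm (central 95%) against 7.67 mm.

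**Step 5: power.** At a true difference of 10.93 with 66 per arm, the noncentrality is 10.93 / 3.88 = 2.82 for both tests. With 130 degrees of freedom power is 79.9%; with 65, under random pairing, it is 79.3%.

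**The case against.** The strongest reply is that the paired test is not the only between-group analysis, and perhaps not the main one. The same sentence first names a repeated-measures ANOVA for the primary outcome. With a group factor, that analysis suits independent arms and does not depend on row order. This stands. A reader might infer that the trial's primary comparison is a paired t test, but the document does not say so. It leaves open which of the two decides, although the t-test clause matches the change contrast in section 2.8.6 more closely.

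A reader might also infer a biased trial. That is not supported. If row order is unrelated to outcome, a paired test on independent normal samples keeps its nominal type I error. Halving the degrees of freedom moves the two-sided critical value only from about 1.98 to 2.00. The 46% figure comes from a data set chosen to sit at P = 0.049, where any small disturbance straddles the threshold. Deliberate sorting could push that P value from about 10⁻²⁹ to 0.16, but nothing in the article suggests that anyone would sort the data.

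Finally, the wording may be a drafting slip. The sample size follows the two-sample formula, the same clause misnames the active arm, and an independent professional statistician is to do the analysis. The trial is also a pilot. These points lower the likely consequence but do not make the text right. The paired t test has its proper within-group use one sentence earlier, so the second use cannot be read as shorthand for the first. Nor is this a detail left to an analysis plan, because the article names a wrong test outright.

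**Conclusion.** The concern holds for the second of the two between-group VAS analyses. As written, that test has no valid definition in this design. The harm is arbitrariness in the SE, CI and P value, together with participants lost when arm sizes differ. It is not systematic bias, and it does not show that the trial is too small. The size is modest: about 0.6 points of power, and no change of conclusion in the example at the design difference. A borderline result, however, could fall on either side of 0.05 according to the ordering of the file. The figures rest on 66 evaluable per arm, SD 22.28 in both arms, normally distributed changes, two-sided 5% and (for reproducing the sample size) 80% power.

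**What to change.** In section 2.8.7.1:

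1. Replace the between-group paired t test with an independent-samples comparison of the VAS change from baseline to week 8, UCHA versus placebo. A baseline-adjusted ANCOVA is an optional refinement and is not needed to cure the defect.
2. Correct SDT to UCHA in that sentence.
3. State which of the two between-group analyses is primary.
4. Keep the paired t test for within-group description only.

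The cost is a sentence or two of text. No new data or participants are needed, and the 82 per arm is unchanged. The article reports recruitment as still under way, with 72 enrolled, so at that stage the correction could be made before database lock.

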#### Inclusion criteria

2.3.1

The inclusion criteria of this study are as follows: patients aged 19 to 59 years who present with CHHF; CHHF score higher than 40 points on the 100-mm visual analog scale (VAS); thermal differences between the palm (PC8) and the upper arm (LU4) may be higher than 0.3°C and differences between anterior of thigh (ST32) and the top of the foot (LR3) may be higher than 2.0°C; symptoms of CHHF in normal temperatures when most individuals do not feel cold or having symptoms of extremely cold hands on cold temperature exposure or individuals who are on the return to a warmer environment but, their cold hands have not completely returned to a normal temperature. Voluntary participation with a signed informed consent form after a detailed explanation of the trial has been obtained.

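### Free improvement: the between-group tests for VAS, skin temperature and WHOQOL-BREF are fixed without the baseline value as covariate, although baseline is measured for all three

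*Protocol article*

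**What the plan says.** All references are to the protocol article.

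- **Primary outcome (section 2.8.6, on sample size).** It is defined as follows: "The change in the CHHF VAS score between baseline and post treatment will be used as the primary outcome measure". Its hypothesis contrasts the mean change in the two arms; one term is defined as "Mean change in the CHHF VAS score between baseline and post treatment in the UCHA group".
- **Primary analysis (Efficacy assessment, 2.8.7.1).** The week-8 comparison of arms on VAS uses a repeated-measures ANOVA, plus what the text calls a paired t test on the mean VAS difference between arms. No covariate is named.
- **Secondary analysis (2.8.7.1).** "the mean differences in ST and WHOQOL-BREF scores between the groups will be analyzed using a repeated-measure ANOVA for ST and an ANOVA", followed for WHOQOL-BREF by a post-hoc analysis. No covariate is named here either.
- **Data available.** The VAS "will be used to assess the severity of CHHF at every visit" (2.8.1.1). Skin temperature is taken at visits 2, 3, 4 and follow-up (2.8.2.1), and WHOQOL-BREF at visits 2, 4 and follow-up (2.8.2.2).
- **Entry rule (Inclusion criteria, 2.3.1).** "CHHF score higher than 40 points on the 100-mm visual analog scale (VAS".

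**The concern.** The section fixes the tests outcome by outcome, so the unadjusted comparison is a stated choice and not a detail left open. Baseline VAS enters only by subtraction in the change score, or perhaps as one level of the repeated-measures ANOVA.

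Two things follow. First, the part of the week-8 variance that baseline predicts is not removed as well as it could be, so the effect estimate has a wider interval than the same patients could give. This matters in a trial meant to inform the power calculation of a larger one. Second, subtracting baseline in full assumes a slope of 1 on baseline. With a smaller slope, an arm that starts higher by chance shows a larger fall for that reason alone.

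A separate wording fault sits in the WHOQOL-BREF sentence. With two arms, a post-hoc test between groups has nothing to compare. If it is meant across visits, an ordinary ANOVA would treat repeated scores from one person as independent.

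**Working it through.** **Inputs from 2.8.6.** Difference 10.93 mm ("the expected mean CHHF VAS score difference in the SDT group is 10.93"); SD 22.28 mm ("the pooled standard deviation (SD) is estimated to be 22.28"); "Considering a dropout rate of 20%, we determine to recruit 82 subjects per arm".

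**Assumed, because the documents do not say.** Two-sided 5% test; 80% power; 22.28 is the SD of the change; equal variance σ² at baseline and week 8; baseline-to-week-8 correlation ρ of 0.3, 0.5 or 0.7.

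**Step 1. Reproduce the plan's figure.** n per arm = 2 × [22.28 × (1.960 + 0.842) / 10.93]² = 65.2. Allowing for dropout, 65.2 / 0.8 = 81.5, which rounds up to 82. The stated size therefore fits an unadjusted comparison at 80% power.

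**Step 2. Variance ratio.** The variance of the change is 2σ²(1 − ρ). The ANCOVA residual variance is σ²(1 − ρ²). Their ratio is (1 + ρ)/2, so the saving is (1 − ρ)/2.

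**Step 3. Power and precision.** The residual SD is 22.28 × √[(1 + ρ)/2]. Power is for a two-sample t test; the one degree of freedom spent on the covariate is ignored.

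| Analysis | Variance saved | Residual SD (mm) | Power, 66 per arm | Power, 82 per arm | 95% CI half-width, 66 per arm (mm) |
|---|---|---|---|---|---|
| Change score | none | 22.28 | 80% | 88% | 7.7 |
| ANCOVA, ρ = 0.3 | 35% | 17.96 | 93% | 97% | 6.2 |
| ANCOVA, ρ = 0.5 | 25% | 19.30 | 90% | 95% | 6.6 |
| ANCOVA, ρ = 0.7 | 15% | 20.54 | 86% | 92% | 7.1 |

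The 66 column is the evaluable number behind the sizing. The 82 column is the intention-to-treat set, which takes in all randomized subjects with the last observation carried forward; no dilution from that imputation is allowed for.

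**Step 4. If 22.28 is a single-visit SD instead.** At 66 per arm (normal approximation), change-score power is 66%, 80% and 95% at ρ = 0.3, 0.5 and 0.7. ANCOVA power is 84%, 90% and 98%.

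**Step 5. Effect of the entry rule.** Let k be the share of baseline variance left after selection, with slope ρ and residual variance σ²(1 − ρ²) unchanged. The change score carries an extra (1 − ρ)²kσ², so the saving is (1 − ρ)²k / [(1 − ρ)²k + 1 − ρ²]. With k = 1 this returns 35%, 25% and 15%. For illustration, a normal baseline with SD 22.28 and mean 40 to 70, cut to the range 40 to 100, keeps about 33 to 47% of its variance. Taking k from 0.3 to 0.5:

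- ρ = 0.3: saving 14 to 21%
- ρ = 0.5: saving 9 to 14%
- ρ = 0.7: saving 5 to 8%

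Here ρ is the correlation before selection. If selection acts on an earlier screening reading, visit-2 VAS is truncated less and the saving lies between these figures and those in Step 3.

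**Step 6. Chance imbalance.** Per 1 mm of baseline difference between arms, the change-score estimate shifts by ρ − 1, that is −0.7, −0.5 or −0.3 mm; the expected ANCOVA shift is zero. If 22.28 were also the baseline SD, the standard error of the baseline difference at 82 per arm would be 22.28 × √(2/82) = 3.5 mm. An imbalance of that size would move the change-score result by about 2.4, 1.7 or 1.0 mm, against a planned effect of 10.93 mm.

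**The case against.** The strongest reply is that nothing here is invalid. Randomization makes the unadjusted comparison unbiased on average, the stated sample size matches it, the trial is exploratory, and a condensed article may leave covariates to a fuller plan. The first three points stand and limit this to an improvement. The last carries less weight, because the article does specify the test for each outcome.

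Other parts of the reply stand and set the limits of the point:

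- A reader might infer that baseline imbalance in VAS is left uncorrected. The documents do not support that: the primary outcome subtracts baseline in full, so imbalance is over-corrected when the slope is below 1.
- A reader might take a 15 to 35% saving as a property of this trial. It is not. The documents give no correlation and do not say what 22.28 is the SD of, and the entry rule can make the saving smaller.
- A reader might infer that selecting patients with high VAS biases the comparison through regression to the mean. It acts on both randomized arms alike and does not.
- The rise from 80% applies to 66 evaluable patients per arm. For the planned intention-to-treat set of 82 the starting point is already about 88%.
- The ratio (1 + ρ)/2 compares ANCOVA with a simple change score. It does not describe the repeated-measures ANOVA, whose handling of baseline the article does not spell out. No size can be given for skin temperature or WHOQOL-BREF, for which the article states no SD.

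**Conclusion.** The point holds as a free gain in precision. The stated between-group tests carry no baseline covariate, while every outcome has a visit-2 value to use. With 22.28 as the SD of change, equal variances and ρ between 0.3 and 0.7, ANCOVA would save 15 to 35% of the variance of a VAS change-score comparison. With baseline variance truncated by the entry rule, the illustrative saving is about 5 to 21%. Under the model used, ANCOVA is the more precise analysis at any ρ below 1, so the direction of the gain does not depend on the assumed values; its size does. The WHOQOL-BREF post-hoc wording needs correction whatever is decided about the covariate.

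**What to change.** In 2.8.7.1, make the primary between-group analysis an ANCOVA of week-8 VAS (or its change, which gives the same treatment effect) on treatment, with visit-2 VAS as covariate. Use the same form for each skin-temperature measure and each WHOQOL-BREF domain, each with its own visit-2 value. Replace the ANOVA with post-hoc analysis for WHOQOL-BREF by this model.

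The cost is analysis wording only: no extra patients, visits or measurements. Because recruitment has begun, record the change in a dated amendment before the data are unblinded, with whatever ethics approval section 2.10 requires for it.
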